### Interventions

Both the experimental and the control groups will receive the standard-of-care, multidisciplinary rehabilitation intervention based on their needs and tolerance, whereas patients in the experimental group will self-administer MT for an additional 30 min. During MT education, the patients will be educated or shown how to perform MT and the patients will complete the recommended exercises on their own for 5 days a week for 4 weeks. The research assistant will aid with setup if needed. As recommended in the standard MT procedures, patients will be asked to remove all jewelry and to sit on the chair or wheelchair in front of the table. A mirror will be placed on the table at a perpendicular angle, and its reflecting surface will face the non-paretic limb. The paretic limb will be positioned behind the mirror, and the non-paretic limb will be placed in front of the reflecting surface of the mirror. Patients will be asked to look at the mirror while doing exercises with the non-paretic limb. This activity will provide visual feedback to the brain like the patient moving the paretic limb. The patients in the MT group will be educated to perform the following several movements on the non-paretic side while looking at the mirror: (1) metacarpophalangeal (MCP) flexion, extension, and abduction; (2) fist and release; (3) wrist ulnar and radial deviations; (4) wrist flexion and extension; (5) forearm pronation and supination; (6) elbow flexion and extension; (7) shoulder flexion; and (8) shoulder abduction. Each movement will be performed for 10 repetitions and 2–3 sets (depending on patient tolerance) for a total of 30 min/session for 5 days a week for a period of 4 weeks. Patients in the experimental group will be given an exercise logbook to record exercise compliance. The logbook will include date, duration of MT, types of exercises (e.g., shoulder movements, elbow movement, wrist movement, and finger movements). Patients will be asked to record the above every single time they do the exercises. Exercise compliance will be considered as adequate if patients complete 80% of MT protocol (e.g., 25 min per day for 4 days a week for 3 weeks).

Participant bias will be minimized by assuring the participant that the quality of rehabilitation will not be affected by group assignment and by explaining that the trial aims to analyze whether the addition of MT education will have an additional beneficial impact on functional outcomes. The research will be initiated in an acute stroke unit and will be carried over in an intensive rehabilitation unit of the same hospital. We are not anticipating any confounding variables at this time during the patient transfer process as this happens within the same hospital and the patients in the experimental group will be self-administering MT only after the regular rehabilitation hours without interrupting any of the exercises or education that are regularly provided by therapists at intensive rehabilitation unit. The mirror for MT will be provided to the patient during the initial assessment (pre-test assessment) that the patient will take it with them to the rehabilitation unit and will be returned at the end of 4 weeks post-assessment.

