### Statistical analysis

#### Data analysis

Data will be analyzed using the SPSS software version 23. Demographic characteristics and baseline scores will be compared using the independent *t*-test and the chi-squared test for continuous variables (such as age and time since stroke) and dichotomous variables (gender, dominance, affected side, and type of lesion), respectively. A two-way repeated analysis of variance (ANOVA) with time and group effects will be used to analyze between-group differences. We will administer both intention-to-treat and per-protocol analyses to determine the effectiveness of the proposed intervention [27]. The level of significance will be set at *P* < 0.05. Patients will be considered as being compliant if they perform at least 80% of the original MT protocol. The compliance will be reported using the four ways recommended by Hawley-Hague et al. (i.e., completion, attendance, duration adherence, and intensity adherence) [28]. In addition, CONSORT will be used to report this RCT to facilitate reading and quality assessment.

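### The worked example of 80% compliance amounts to half of the prescribed mirror therapy minutes and 60% of the sessions, so the percentage and its example give two different compliance rules

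*Protocol article*

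**What the plan says.** The Interventions section of the protocol article sets the MT programme as exercises done "for a total of 30 min/session for 5 days a week for a period of 4 weeks". Patients in the experimental group keep a logbook: "The logbook will include date, duration of MT, types of exercises". The same section then defines adequate compliance and illustrates it: compliance is "adequate if patients complete 80% of MT protocol (e.g., 25 min per day for 4 days a week for 3 weeks".

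The Data analysis section repeats the threshold without the illustration: "Patients will be considered as being compliant if they perform at least 80% of the original MT protocol". Shortly before that sentence it states: "We will administer both intention-to-treat and per-protocol analyses to determine the effectiveness of the proposed intervention". Compliance is also to be reported in four ways, namely "completion, attendance, duration adherence, and intensity adherence".

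The article gives no other criterion for membership of the per-protocol set. It also does not say whether the 80% refers to minutes, to sessions, or to each component of the schedule.

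**The concern.** An example of reaching a threshold has to reach it. This one trims minutes per day, days per week and number of weeks all at once, by between a sixth and a quarter each, and the three reductions multiply. The result lies well below 80% of the programme, yet it is the only operational guidance on how the percentage is to be read.

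Two things depend on the rule. One is the compliance rate, which matters for a self-administered treatment recorded by the patients themselves. The other, on the natural reading, is who enters the per-protocol analysis. With two inconsistent versions of the rule in the document, a patient can be compliant under one and not under the other, and the version could be chosen after the logbooks have been seen.

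**Working it through.** **Inputs.** All come from the Interventions section, except the restated threshold (Data analysis) and the size of the MT group, 18 (Sample size estimates).

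- Prescribed: 30 min per session, 5 days a week, 4 weeks.
- Example: 25 min per day, 4 days a week, 3 weeks.
- Threshold: 80%, restated in Data analysis as at least 80%.

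**Whole programme**

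- Prescribed minutes: 30 × 5 × 4 = 600. Prescribed sessions: 5 × 4 = 20.
- Example minutes: 25 × 4 × 3 = 300. Example sessions: 4 × 3 = 12.
- Share of minutes: 300/600 = 50%.
- Share of sessions: 12/20 = 60%.
- The stated 80%: 0.80 × 600 = 480 min, or 0.80 × 20 = 16 sessions. The example is 180 min and 4 sessions short.

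**Attempt to reproduce the stated 80%**

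| Measure | Calculation | Result |
|---|---|---|
| Minutes per session alone | 25/30 | 83.3% |
| Days per week alone | 4/5 | 80.0% |
| Weeks alone | 3/4 | 75.0% |
| Mean of the three | (83.3 + 80.0 + 75.0)/3 | 79.4% |
| Minutes × days | 100/150 | 66.7% |
| Minutes × weeks | 75/120 | 62.5% |
| Days × weeks (sessions) | 12/20 | 60.0% |
| All three (total minutes) | 300/600 | 50.0% |

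No cumulative measure comes near 80%. Two of the three single components reach it, but the number of weeks does not. A rule requiring at least 80% on every component would therefore also reject the example. The mean of the three stops just short.

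**How the two versions classify patients.** The example is a pattern (a minimum per day, per week and in weeks), not a total of minutes. Some illustrative logbooks, with 80% taken as total minutes:

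| Logged | Minutes | Meets the example's pattern? | At least 480 min? |
|---|---|---|---|
| 25 min, 4 days, 3 weeks | 300 (50%) | yes | no |
| 30 min, 5 days, 3 weeks | 450 (75%) | yes | no |
| Ten 30-min sessions | 300 (50%) | no, 10 sessions against 12 | no |
| Twenty 20-min sessions | 400 (67%) | no, under 25 min | no |
| Twenty 24-min sessions | 480 (80%) | no, under 25 min | yes |

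The versions disagree in both directions. If all 18 MT patients are assessed, each reclassified patient moves the compliance rate by 1/18 = 5.6 percentage points.

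**The case against.** The best defence is that the authors meant roughly 80% of each component and rounded to convenient numbers. The values 83%, 80% and 75%, averaging 79.4%, suggest that this is how the example arose. The plan to report several separate aspects of adherence fits such thinking. On that view the main fault is that the unit of the percentage was never stated. This is probably the right explanation, but it does not rescue the text: 3 of 4 weeks is 75%, below the stated minimum, and the Data analysis section applies the threshold to the original protocol without splitting it into components.

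It is also fair to say that the illustration is a parenthesis, that the analysis section carries only the bare percentage, and that the reach is limited. Only the MT group keeps a logbook, so at most 18 patients are classified by it. Reporting adherence in four ways should make much of the actual exposure visible. Randomisation, sample size, outcome assessment and the intention-to-treat analysis are untouched. All of this stands and limits the size of the point.

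Three stronger readings are tempting and go too far.

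- A reader might infer that half-dose patients will enter the per-protocol set. The document does not say so. That requires the example to be the rule applied and the set to be defined by compliance. The second condition is the natural reading, but it is implied only, and the bare 80% in minutes would keep such patients out.
- A reader might infer that everyone logging 300 to 479 minutes is compliant by the example. The logbooks of ten 30-minute and twenty 20-minute sessions show otherwise.
- A reader might infer that replacing 80% by 50% would settle the matter. That describes the example only if the unit is total minutes; in sessions it is 60%, and the daily minimum would be lost.

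**Conclusion.** The contradiction is certain and rests only on the protocol's own figures. The example given for 80% is 50% of the prescribed minutes and 60% of the prescribed sessions, and it fails 80% on the number of weeks even component by component. Nothing else in the article repairs it. It is a stated threshold that conflicts with its own illustration, not a detail left to an analysis plan.

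The consequence is conditional. If the example is applied and the per-protocol set is the compliant patients, patients with as little as half of the prescribed minutes could be counted as compliant, where 80% of minutes would require 480. How many patients this would affect, and how far it would shift the per-protocol result, cannot be known from the document. The effect is confined to compliance reporting and, by implication, the per-protocol analysis.

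**What to change.** Reconcile the Interventions and Data analysis sections into one compliance rule, worded the same in both places.

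- State the unit of the percentage. Logged minutes out of 600 is one workable choice, since the logbook already records date and duration; sessions out of 20 or a component-by-component rule are also possible.
- Make the percentage and the example agree in that unit, either by correcting or deleting the example or by restating the percentage. Which threshold to adopt is for the investigators.
- Say in words whether the per-protocol set in the MT group is defined by this rule.

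The cost is a sentence or two and no new data collection. The Trial status section reports that no patients had been recruited when it was written, so the rule can be fixed before the first patient. The one downside is that, if 80% of minutes is kept, the per-protocol set may be smaller than under the example.

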## Material and methods

### Study design

A single-center, prospective, randomized, open-label, controlled trial with blinded outcome evaluation (PROBE design) will be used to evaluate the effectiveness of self-administered MT on upper extremity functions of acute/or early sub-acute stroke patients.

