### Group assignment

#### Sample size estimates

The sample size and effect size were calculated based on a previously published study [24], using the G* power software. A sample of 18 will be required in each group to detect a difference in the primary outcome measure (FMA-UE) with an effect size (Cohen’s d) of 1.15 and a statistical power of 0.80 at a one-sided type one error of 0.05.

Based on the above calculation, a total of 36 patients will be recruited and assigned to the MT (n = 18) or control group (n =18) using a random sampling method. Randomization will be done prior to the baseline assessment with a statistical software program that generates this sequence. Random numbers will be assigned according to the order of patients’ admission to the hospital. To *conceal allocation*, random group allotment will be managed by a social worker who will not be involved in the assessment or intervention to minimize the confounding and contamination. Refer to Fig. 1 for the study process.

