### Blinding

Pre- and post-test assessments will be performed by a physiotherapist who will be blinded to group allocation (assessor blinding). Patient education will be provided by a research assistant who will neither be involved in outcome assessment nor with implementing regular rehabilitation interventions. The research assistant will ensure that the patient understands the parameters of the exercise intervention, mirror placement, and unilateral arm execution (nonparalytic arm should be moved and not the paralyzed arm) and masters the MT technique.

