### Participant timeline

Participant timeline was developed according to the SPIRIT guideline and is presented in Table 3.

**Table 3 Tab3:** Timeline of screening, recruitment, randomization, interventions, and assessments

Time point	Study period		
	0 week (w)	4 w	Closeout (4 w)
Enrollment			
Eligibility screen	x		
Informed consent	x		
Allocation	x		
Intervention			
Experimental group	x	x	
Control group	x	x	
Assessments			
Demographics	x		
FMA-UE	x	x	
WMFT	x	x	
MBI	x	x	

*FAM-UE* Fugl-Meyer Assessment-upper extremity, *WMFT* Wolf Motor Function Test, *MBI* Modified Barthel Index

Rehabilitation interventions are crucial during the first 4 weeks post-stroke as it is a critical time for neural plasticity and recovery [17]. Therefore, the present study will be initiated within 48 to 72 h of patient admission in the acute care unit and will be continued for 4 weeks following the initial assessment. Following admission to an acute stroke unit, screening and informed consent and baseline outcome assessments will be completed within 48 to 72 h. The mirror therapy education will commence immediately after the baseline assessment and end in 4 weeks.

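### Handing the mirror over during the pre-test assessment, and taking it back around the post-test, is likely to show allocation to the only role described as blinded

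*Protocol article*

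**What the plan says.** All references are to the protocol article.

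- **Study design** describes a "randomized, open-label, controlled trial with blinded outcome evaluation (PROBE design".
- **Blinding** names the blinded role: "Pre- and post-test assessments will be performed by a physiotherapist who will be blinded to group allocation (assessor blinding". It gives the teaching of mirror therapy (MT) to someone else: "Patient education will be provided by a research assistant who will neither be involved in outcome assessment nor with implementing regular rehabilitation interventions".
- **Sample size estimates** places allocation before the first scores are taken: "Randomization will be done prior to the baseline assessment with a statistical software program that generates this sequence".
- **Interventions** confines MT to one arm: "patients in the experimental group will self-administer MT for an additional 30 min". At its end, the same section gives the timing of the mirror: "The mirror for MT will be provided to the patient during the initial assessment (pre-test assessment". The patient takes it to the rehabilitation unit, and it "will be returned at the end of 4 weeks post-assessment".
- **Participant timeline** says: "The mirror therapy education will commence immediately after the baseline assessment and end in 4 weeks".

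**The concern.** The mirror identifies the arm. The text has it change hands within the session run by the person who must not know the arm, after the arm has been fixed. Nothing in the article gives control patients a mirror, screens the mirror from the assessor, or requires it to be put away before the second assessment.

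The stake is detection bias. Patients know their group, so the assessor's ignorance of it is the design's main protection for the rated outcomes. According to Outcome measures and data collection, the assessing physiotherapist rates both primary measures (FMA-UE and WMFT) and the secondary one (MBI). The authors treat this feature as a quality criterion themselves: Table 2 rates two of the five earlier trials at high risk on blinding of outcome assessment.

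**Working it through.** The point depends on no stated figure, so the check sets the sections side by side.

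1. **Is the arm known at the pre-test?** Yes. Sample size estimates puts randomization before the baseline assessment.
2. **Does the mirror identify the arm?** Yes. Under Interventions only the experimental group performs MT, and no section gives a mirror to control patients.
3. **When is it handed over?** Interventions says during the initial assessment and adds in brackets that this is the pre-test. Blinding has the blinded physiotherapist perform the pre-test.
4. **Does the rest of the article point the same way?** Not entirely. Blinding gives MT teaching to a research assistant outside outcome assessment, and Participant timeline starts that teaching once baseline is done. Both suggest that the MT material should come after the assessment. The hand-over sentence places it inside.
5. **When does it come back?** The wording can mean at the post-test visit, or four weeks after the first assessment. On either reading the patient keeps the mirror until about the post-test, and nothing requires its removal beforehand.
6. **Which scores are exposed?** The planned analysis is a two-way repeated-measures ANOVA with two time points. Its group-by-time contrast is the difference between arms in mean change:

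   effect = (MT post − MT pre) − (control post − control pre).

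   If knowledge of allocation shifted MT-arm ratings by a at the pre-test and b at the post-test, with control ratings unaffected, the effect would be biased by b − a. A lower baseline rating (a < 0) and a higher 4-week rating (b > 0) both favour MT.
7. **Does the timing within the baseline session matter?** Partly. A hand-over after scoring but with the assessor present would leave a = 0. If the same physiotherapist then does the post-test, b can still differ from zero even with the mirror out of sight at that visit. The article speaks of the assessor in both singular and plural, so it does not settle whether one person does both.

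No size follows. It would need the chance that the assessor learns the arm and the scoring shift that results, and the article gives neither.

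**The case against.** The strongest reply is that the hand-over sentence is passive. It does not say who gives the mirror, where, or whether the assessor is present. The research assistant teaches MT and helps with setup, and the teaching starts after baseline, so the assistant could supply the mirror around the baseline visit without the assessor seeing it. The term initial assessment may also mean the visit as a whole, since demographic data are collected under a similar label. The flow chart of the study process is not visible in the text available.

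Much of this stands, and it rules out three stronger readings.

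- A reader might infer that the plan demonstrably unblinds the assessor, or that the Blinding and Interventions sections cannot both be followed. The documents do not support that. The two can be reconciled if the hand-over is kept from the assessor, although no sentence says that it will be.
- A reader might infer that the mirror is in view at both assessments. No section says where the post-test is held or where the mirror is during it, so the post-test part is only a possibility.
- A reader might try to size the bias by setting an assumed shift of 1 to 2 FMA-UE points against the pooled difference of 4.32 in the Critical review (1/4.32 = 23%, 2/4.32 = 46%). The shift has no basis in the documents, and 4.32 comes from a review of other trials. It is not this trial's design effect. No weight should be put on these percentages.

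The reply does not remove the sentence itself. It is a stated step, so this is more than detail that a condensed article leaves to a fuller document. Its plain wording puts the mirror inside the blinded session.

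**Conclusion.** The concern holds as a likely exposure of allocation through a badly timed step. It does not hold as proven unblinding. Followed as written, the hand-over sentence is likely to show the arm to the only role described as blinded, most clearly at baseline and possibly at the post-test. It also fits poorly with MT education that starts after baseline.

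This rests on two inferences: that the word during carries its ordinary meaning, and that the assessor is present in a session that the assessor runs. Bias from a lower baseline or a higher 4-week rating in the MT arm would favour MT, but its size cannot be estimated from the documents. The correction is worth making before enrolment, because an analysis cannot restore assessor blinding once it is lost.

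**What to change.** Amend the end of the Interventions section as follows, and bring Blinding and Participant timeline into line with it.

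- The research assistant gives the patient the mirror and the logbook only after the baseline assessment is complete, and out of the assessor's presence.
- The research assistant collects both, or makes sure they are out of sight, before the 4-week assessment begins.
- Patients are asked not to tell the assessor which group they are in.

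The cost is a minor change in the order of steps and one added instruction to patients. No staff are added, because the research assistant already teaches MT and helps with setup. Trial status reports that no patients had been recruited at the date it gives, so on that information the change could be in place before the first patient.

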### Outcome measures and data collection

The primary outcome measures of interest are the level of upper limb motor impairment and functional performance. These variables will be measured using the Fugl-Meyer Assessment-upper extremity (FMA-UE) and the Wolf Motor Function Test (WMFT), respectively. Both FMA-UE and WMFT are reliable and valid outcome measures and are used consistently in MT research [25]. Moreover, the Stroke Edge Task Force of the Academy of Neurological Physical Therapy (American Physical Therapy Association) recommends FMA-UE and WMFT for patients who have had a stroke and who are undergoing acute care [26]. The secondary outcome measure will be ADL measured by the Modified Barthel Index (MBI), a reliable and valid tool for assessing ADL in stroke survivors and used in MT research.

A physiotherapist will assess the above outcome measures twice: (1) pre-test assessment at the beginning of the trial and (2) post-test assessment at the end of the trial. Before the study, the assessor will be trained in assessing all outcome measures and will be tested with two patients to assure standardization. The assessors will be trained by one of the investigators of this study (VR) who is a physiotherapist specialized in stroke rehabilitation and experienced in administering the above outcome measures. In addition, demographic characteristics, such as age, gender, handedness, Alpha-FIM score, Brunnstrom stages of motor recovery, type of lesion, side of hemiplegia, and the onset of stroke, will be collected during the initial assessments (Fig. 2).

